**Methods:**

In this cluster randomized, single-blinded, controlled trial, each cluster consists of at least two occupational therapists, a manager, and a physician working at Dutch healthcare organizations that deliver community occupational therapy. Forty-five clusters, stratified by healthcare setting (nursing home, hospital, mental health service), have been allocated randomly to either the intervention group (CI strategy) or the control group (ED strategy). The study population consists of the professionals included in each cluster and community-dwelling people with dementia and their caregivers. The primary outcome measures are the use of community OT, the adherence of OTs to the COTiD program, and the cost effectiveness of implementing the COTiD program in outpatient care. Secondary outcome measures are patient and caregiver outcomes and knowledge of managers, physicians and OTs about the COTiD program.

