## Methods/Design

### Trial Design

A single blinded, cluster randomized controlled design is used to compare the effectiveness and cost-effectiveness of the two implementation strategies. An independent statistician stratified the clusters by type of setting (hospital, nursing home, and mental health services) and randomized them to either the control (educational strategy) or experimental group (the combined implementation strategy) (see Figure 1). Clusters were randomized using a 2 to 1 (control vs. experimental) ratio, as it is expected that physicians in the experimental group will refer more clients for this community occupational therapy intervention than those in the control group. This assumption implies that more clusters are needed in the control group to collect data from a sufficient number of client-caregiver couples. At the time of randomization 45 organizations agreed to participate in the study.

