**Figure 1 F1:**
[figure not shown]
Flow Chart of the Study Design.

Three research assistants blinded for group allocation collected all data. Client-caregiver couples are not aware of the group allocation of their healthcare professionals (physician and occupational therapist). A complete double blinded trial is not possible as the participating professionals are aware of the implementation strategy they received.

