#### Client-caregiver couples

Clients with dementia and their caregiver are enrolled during the first year of the study. They are approached to participate in the study by physicians of one of the study clusters.

Eligibility criteria for client-caregiver couples:

1. The client has mild to moderate dementia (MMSE score 10-24, DSM IV criteria for dementia)

2. Clients are referred to an occupational therapist participating in the study

3. The client lives at home at the time of inclusion

4. The informal caregiver takes care of the client at least two times a week

5. The client is not diagnosed with depression (Geriatric Depression Scale 30 >12)

6. The client has no severe behavioral or psychological symptoms (BPSD)

7. The client has no severe illness preventing participation

8. The caregiver has no severe illness preventing participation

9. Both client and caregiver consent to participate

Participation of client-caregiver couples is discontinued when severe BPSD develops, the client is permanently admitted to an institution, or the client or caregiver no longer wish to participate.

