**Caregiver**									
Demographics			✓	Survey	✓				
Quality of Life	✓			Dqol	✓		✓		✓
Quality of life	✓	✓		EQ-5D	✓		✓		✓
Clients execution of daily activities	✓			IDDD	✓		✓		✓
Sense of competence	✓			SCQ	✓		✓		✓
Problems in daily life	✓			COPM	✓		✓		✓
Depression			✓	CES-D	✓		✓		✓
Healthcare costs	✓	✓		RUD lite basic	✓				
Healthcare costs	✓	✓		RUD lite follow-up		✓	✓	✓	✓

SO = secondary outcome; EE = economic evaluation; BG = background; T0 = baseline measure; T1 = 3-month follow-up measure; T2 = 6-month follow-up measure; T3 = 9 -month follow-up measure; T4 = 12-month follow-up measure; GDS = Geriatric Depression Scale; MMSE = Mini Mental State Exam; Dqol = Dementia Quality of Life Scale; AMPS = Assessment of Motor and Processing Skills; EQ-5 D = EuroQol 5D; COPM = Canadian Occupational Performance Measure; IDDD = Interview for Deterioration of Daily Activities in Dementia; SCQ = Sense of Competence Questionnaire; CES-D = Center for Epidemiologic Studies Depression Scale; RUD Lite basic = Resource Utilisation in Dementia - Baseline questionnaire; RUD Lite follow-up = Resource Utilisation in Dementia - follow-up questionnaire

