### Statistical methods

Random effects regression models will be used to evaluate differences in adherence and in use of community OT between the experimental and control group. Baseline scores will be used as covariates and type of setting and OT will be used as random factors.

Differences in knowledge between professionals (occupational therapists, physicians, and managers) in the experimental and control group will be evaluated using t-tests, unless data have a substantially skew distribution in which case non-parametric tests are used. Random effect regression models for repeated measures will be used to evaluate differences in knowledge at different times of measurement within each group and between groups. The influence of several characteristics of the professionals on their knowledge level will be evaluated using ANOVA (e.g. sex) and linear regression (e.g. age, years of professional experience).

Random effects regression models will be used for analyses of covariance of the outcome measures (AMPS process [23], IDDD performance [24], DQOL [25], SCQ [26], EQ-5 D [27] at 6 and 12 months (see Table 2)) based on an intention-to-treat analysis of all available data. Treatment differences between baseline and 6 months and baseline and 12 months will be computed by analysis of covariance, with age, sex, relation to patient, and baseline scores on the co-morbidity, MMSE scores, GDS scores, and outcome variable at baseline as covariates.

For all tests significance will be tested using two-sided tests with an alpha level of.05.

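### Caregiver outcomes are adjusted for the client's mood and cognition but not for the caregiver's own baseline depression score, and setting is not named for the couple models; the gain from adding both is probably small but costs nothing

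*Protocol article*

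**What the plan says.** For the couple-level outcomes the Statistical methods section of the protocol article states: "Random effects regression models will be used for analyses of covariance of the outcome measures". It names AMPS process, IDDD performance, DQOL, SCQ and EQ-5D at 6 and 12 months. One adjustment set serves them all: "with age, sex, relation to patient, and baseline scores on the co-morbidity, MMSE scores, GDS scores, and outcome variable at baseline as covariates". The list does not say whose age, sex or co-morbidity is meant, although Table 2 records demographics for both members of the couple.

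Table 2 places the GDS and MMSE in the client block only, as background measures at T0. It places the CES-D in the caregiver block, also as background, at T0, 6 months and 12 months ("CES-D = Center for Epidemiologic Studies Depression Scale"). The article gives the CES-D no other role in the analysis.

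Under Trial Design, an independent statistician "stratified the clusters by type of setting (hospital, nursing home, and mental health services") before randomising them. Statistical methods names type of setting as a random factor for the adherence and use models. It does not name setting for the couple models.

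**The concern.** SCQ, caregiver Dqol and caregiver EQ-5D describe the caregiver. Besides their own baseline value, they are adjusted for another person's mood and cognition but not for the caregiver's own mood, although that was measured at the same visit. The eligibility criteria restrict the client's MMSE and depression, so those covariates have a narrowed range. No criterion restricts caregiver depression.

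Two things could be at stake. The first is precision, if baseline CES-D predicts follow-up beyond what the outcome's own baseline predicts. The second is protection against chance or selection imbalance. Clusters were already randomised when couples began to enter, and of the couples the article says: "They are approached to participate in the study by physicians of one of the study clusters". It also says that "participating professionals are aware of the implementation strategy they received". The experimental strategy sets out to motivate physicians to refer. Balance between the couples in the two arms is therefore not protected as it would be had couples been randomised individually. Similarly, if the stratification factor is absent from the couple models, any variation between settings stays in the error.

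**Working it through.** **The plan's own figures.** The article gives no power or sample size for any caregiver outcome, so there is no figure to reproduce on this point. Its two power statements concern the primary endpoints. Both reproduce with a two-sided 0.05 test of two proportions: 81.3% for adherence (20% vs 50%, 57 vs 29 effective subjects; stated 80%) and 99.7% for community OT use (5% vs 25%, 204 vs 102; stated 99%). Neither bears on the covariates.

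**Precision: inputs.** The article gives no correlations, so these are assumptions (CES-D scored so that its correlations are positive):
- *r*, outcome at baseline with outcome at follow-up: 0.5 to 0.8
- *c1*, baseline CES-D with outcome at follow-up: 0.3 to 0.5
- *c0*, baseline CES-D with outcome at baseline: 0.3 to 0.6

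**Formula.** With the outcome baseline alone, the residual variance share is 1 − *r*². Adding CES-D multiplies it by

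ratio = 1 − (*c1* − *r·c0*)² / [(1 − *c0*²)(1 − *r*²)].

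A comparison with 80% power without CES-D then has power Φ((1.96 + 0.8416)/√ratio − 1.96).

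**Results.**
- Middle case (*r* = 0.6, *c1* = 0.4, *c0* = 0.5): numerator (0.4 − 0.30)² = 0.01; denominator 0.75 × 0.64 = 0.48; ratio 0.979. Variance falls by 2%, and power goes from 80% to 80.8%.
- Largest (0.8, 0.5, 0.3): (0.5 − 0.24)² = 0.0676; 0.91 × 0.36 = 0.3276; ratio 0.794. Variance falls by 21%, and power goes to 88%.
- Smallest (for example 0.5, 0.3, 0.6): *c1* = *r·c0* = 0.30, so the gain is zero.
- On a grid in steps of 0.1 (4 × 3 × 4 = 48 combinations), 38 give a fall below 10%.

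**Allowing for clustering.** Take ICC = 0.05, which the article assumes for other endpoints, and 8 couples per cluster, the eligibility minimum. The variance of a cluster mean is then 0.05 + 0.95/8 = 0.16875. If CES-D explains only the within-cluster part:

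| Fall in within-cluster variance | Variance of cluster mean | SE falls by | SE fall ignoring clustering |
|---|---|---|---|
| 2% | 0.05 + 0.98 × 0.11875 = 0.16638 | 0.7% | 1.0% |
| 10% | 0.05 + 0.90 × 0.11875 = 0.15688 | 3.6% | 5.1% |
| 21% | 0.05 + 0.79 × 0.11875 = 0.14381 | 7.7% | 11.1% |

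**Imbalance.** If the arms differ by 0.2 SD in baseline CES-D (assumed), omitting it shifts the adjusted effect by 0.2 × *b*, where *b* = (*c1* − *r·c0*)/(1 − *c0*²) and the outcome baseline is balanced. In the middle case *b* = 0.10/0.75 = 0.133, a shift of 0.027 SD. If the outcome baseline is imbalanced in proportion, the shift is 0.027 × (1 − 0.25) = 0.020 SD. The largest shift on the grid is 0.2 × 0.385 = 0.077 SD (*r* = 0.5, *c1* = 0.5, *c0* = 0.3). With no imbalance it is zero.

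**Setting.** The documents give nothing from which to size the between-setting variance of the couple outcomes, so no figure is offered.

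**The case against.** The strongest reply is that this is a choice, not an error. The list is prespecified, nothing in the article promises adjustment for CES-D, and nothing is contradicted. The client's cognition and mood are sensible predictors of a caregiver's sense of competence. The outcomes are secondary: "Secondary outcome measures are patient and caregiver outcomes and knowledge of managers, physicians and OTs about the COTiD program". Above all, the list includes each outcome's own baseline, which captures much of what CES-D would explain. All of this stands, and it is why the point is minor.

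Three stronger inferences are tempting, and the documents do not support them.
- A reader might infer that the omission demonstrably loses precision. With no correlations given, a gain of zero is within the range.
- A reader might infer that it biases the caregiver comparisons. Leaving out a prognostic covariate does no such thing without an imbalance. The recruitment route makes one possible, but none is shown. Nor would adjustment remove it all: a linear term in one score measured with error leaves a remainder and does not touch unmeasured selection.
- A reader might infer that setting has been dropped from the couple models. They are described as random effects models whose random terms a condensed article need not list, so setting may be present but unnamed.

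The reply does not dispose of the asymmetry itself. The covariate list is stated in the article, not left to another document. It turns the client's background mood score into a covariate and gives no reason for leaving out the caregiver's parallel score.

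**Conclusion.** The point holds as a minor improvement to the analysis of secondary outcomes. One list serves two kinds of respondent; for caregiver outcomes it omits a relevant baseline measure already in hand, and it leaves unclear whose age, sex and co-morbidity are used. The benefit of adding CES-D is possible and probably small: a 0% to 21% cut in residual variance, about 2% in the middle case, with correspondingly less effect on the standard error if only within-cluster variance is explained. Protection against a 0.2 SD imbalance in caregiver mood is worth about 0.02 to 0.03 SD in the middle case and at most about 0.08 SD. These sizes rest on the assumed correlations, imbalance, ICC and cluster size, not on trial data. For setting, the defect is that the couple models do not name it although it was a stratum; its effect cannot be sized. The primary analyses and their power are unaffected.

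**What to change.** Before any analysis by arm, replace the single list with two prespecified sets.
- **Caregiver outcomes** (SCQ, caregiver Dqol, caregiver EQ-5D): keep the baseline value of the outcome, add baseline CES-D, and use the caregiver's own age and sex. Only the T0 score may be used; the 6- and 12-month scores come after allocation and could be affected by it.
- **Client outcomes**: keep the present list, stating that age and sex are the client's. IDDD appears in the caregiver block but rates the client's activities, so say which set it takes.
- **All couple outcomes**: state that type of setting (three levels) is in the model, and say whose co-morbidity is meant.

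If the CES-D is meant to be descriptive only, a sentence giving the reason would serve instead of adding it. The cost is a few lines in the analysis plan, with no new data and no change to conduct.

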### Economic evaluation

One of the primary questions of this study concerns the difference in cost-effectiveness between the CI-strategy and the ED-strategy strategy regarding adherence of OTs to the COTiD program. Secondary, the study is designed to evaluate the difference in cost-effectiveness between the implementation strategies with regard to the quality of life of clients with dementia and their caregiver. To evaluate these questions an economic evaluation will be executed from a societal viewpoint. This implies that both costs within and outside the healthcare system, are included in the evaluations [28,29].

#### Costs

Table 3 displays data collected on costs of the implementation strategies. All costs made for the execution and development of the two strategies are registered. Developmental costs are calculated using the annuitization procedure [28]. Because of the unbalanced design (more clusters are randomly assigned to the control group) the calculation of costs will not be protocol driven. This prevents differences in costs between groups due to an unequal number of OTs, physicians, managers and/or clients.

**Table 3 T3:** Cost data collected on the implementation strategies

Costs/Time	T0	T1	T2
**Occupational Therapists (OTs)**		✓	
Time spend on post-graduate course		✓	
Time spend on the implementation training		✓	
Time spend on coaching on the job		✓	✓
Time spend on regional meetings		✓	✓
			

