#### The Combined Implementation Strategy

The CI-strategy is a multifaceted strategy that, beside the post-graduate course for OTs, consists of additional interventions toward occupational therapists and interventions toward physicians and managers:

*1. Implementation training days*. The training days focus on refreshing and/or increasing professional skills regarding execution of the COTiD program and skills regarding promotion of the COTiD program.

*2. Coaching on the job*. Coaching sessions are held to address individual problems experienced by occupational therapists regarding the implementation of the COTiD program. Between five and seven coaching sessions are scheduled depending on the OTs individual needs.

*3. Regional meetings*. These meetings are provided to create an opportunity for OTs to discuss practice issues with OT colleagues from the same region. Four regional meetings are organized during one year.

*4. Web-based reporting system and discussion forum*. An electronic reporting system was developed to guide OTs through the steps of the COTiD program. Treatment reports can be created for every client-caregiver couple. In addition, a link to a discussion platform is provided through which OTs are able to share experiences and exchange helpful resources.

*5. Website and newsletters*. Information on the COTiD program, its effectiveness, and cost-effectiveness is provided to physicians, managers, and OTs. The information is presented through a website and four newsletters. Information is adjusted for each group of professionals, to meet the specific needs of the group.

*6. Telephone calls*. Managers and physicians are contacted by phone at least once to evaluate if they have questions on the COTiD program and the implementation in practice. The goal is to provide more insight in the COTiD program and to motivate managers to facilitate the program and motivate physicians to refer clients to treatment according to the COTiD program. The ultimate goal is to increase the number of referrals to community OT.

Two OTs who are experienced teachers, have extensive experience in using the COTiD program, and are trained in motivational interviewing provide the implementation training, coaching, and organize the regional meetings.

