**Physicians**			
Time spend on reading newsletters		✓	✓
Time spend on reading on the website		✓	✓
Time spend on motivational phone calls		✓	✓
			

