**Managers**			
Time spend on reading newsletters		✓	✓
Time spend on reading on the website		✓	✓
Time spend on motivational phone calls		✓	✓
			

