**Development & execution***			
Post-graduate course - developmental & execution costs			
Implementation training - developmental & execution costs			
Regional meetings - developmental & execution costs			
Coaching on the job - developmental & execution costs			
Web-based system - developmental costs			
COTiD-program website - developmental costs			
Newsletters - preparation costs			
Motivational phone calls - preparation & execution costs			

T0 = baseline measure; T1 = 6 month follow-up measure; T2 = 12 month follow-up measure/* All development and execution costs are registered throughout the entire study period.

Healthcare costs made by client-caregiver couples are collected using the Lite version of the resource utilization in dementia instrument (RUD Lite) [30]. The RUD Lite is used every 3 months during a one year period. Data on both the caregiver and client are provided by the informal caregiver. Caregivers are asked to provide information about the preceding month as retrieving information over a longer period is often unreliable. An algorithm will be used to get a reliable estimate for the total period of three months. If available, market prices are used to calculate costs. If these are not available standard cost-prices are used as identified in the Dutch manual for costs in economic evaluations [31].

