#### Exposure to the CI-strategy

Actual exposure of healthcare professionals to the CI-strategy is evaluated using a variety of methods. Attendance and exposure to all parts of the CI-intervention is registered for each healthcare professional. The characteristics of all interventions (e.g. frequencies, duration, medium, content etc.) were registered on recording forms. The research team has unlimited access to the web-based-system and discussion platform to collect data on the frequencies these systems are used. Exposure to the website and newsletters was evaluated using a close-ended questionnaire. This questionnaire addresses the frequency participants visited the educational website and the number of newsletters read.

Actions undertaken by the research team regarding both the CI-strategy and the research process are registered in a research log.

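### Table 3 lists no OT time for the newsletters, website, forum or web-based reporting system, so as listed it would tend to understate the incremental cost of the CI strategy

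*Protocol article*

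**What the plan says.** On scope, the Costs section states "All costs made for the execution and development of the two strategies are registered" and introduces the table with "Table 3 displays data collected on costs of the implementation strategies". The footnote to Table 3 repeats that development and execution costs are all registered, over the whole study period. The Economic evaluation section adopts a societal viewpoint and makes cost-effectiveness with respect to OT adherence one of the primary questions.

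On content, the section on the Combined Implementation Strategy gives OTs the web-based reporting system and discussion forum (element 4). For the website and four newsletters (element 5) it says "Information on the COTiD program, its effectiveness, and cost-effectiveness is provided to physicians, managers, and OTs".

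On what is recorded, the OT block of Table 3 has four time rows: the post-graduate course, the implementation training, coaching, and "Time spend on regional meetings". The physician and manager blocks each contain "Time spend on reading newsletters" and "Time spend on reading on the website", both ticked at 6 and 12 months. In the development and execution block one row reads "Web-based system - developmental costs". The website row is likewise limited to development and the newsletter row to preparation, while the other five rows also name execution.

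**The concern.** The plan treats reading a newsletter or visiting the website as a cost worth recording for physicians and managers. It lists no such cost for the OTs, who receive the same material and whose adherence is the effect in the ratio. Nobody's time on the reporting system or forum is listed. That does not fit the claim that all costs are registered, nor a societal viewpoint, under which professionals' time counts.

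The direction matters. Under the Educational Strategy, professionals receive no intervention during the study period, so net extra time on these elements can arise only in the CI arm. Leaving it out lowers incremental cost, and with it the cost per extra percentage adherence. That ratio answers one of the trial's primary questions.

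**Working it through.** The document states no figure for strategy cost, so there is none to reproduce. The check is a match of OT-facing elements to table rows, followed by an illustration of size.

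**1. Matching the elements to Table 3**

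| Element given to OTs in the CI arm | OT time row? | Same item recorded for physicians and managers? |
|---|---|---|
| Implementation training days | yes | not applicable |
| Coaching on the job | yes | not applicable |
| Regional meetings | yes | not applicable |
| Web-based reporting system | no | not applicable |
| Discussion forum | no | not applicable |
| Website | no | yes |
| Newsletters | no | yes |

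Three of the seven have a row and four do not. The post-graduate course also has a row, but both arms receive it.

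**2. Is the time picked up elsewhere?** The process evaluation says "The research team has unlimited access to the web-based-system and discussion platform to collect data on the frequencies these systems are used". It also has a questionnaire on how often the website was visited and how many newsletters were read. These are frequencies, not time, and no link to costing is stated.

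**3. Costed OT time, for scale.** From the document: two training days, five to seven coaching sessions (midpoint 6), four regional meetings. Assumed, because the document gives no durations: 8 h per training day, 1 h per coaching session, 2.5 h per meeting.

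2 × 8 + 6 × 1 + 4 × 2.5 = 16 + 6 + 10 = 32 h per OT.

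**4. Couples per OT.** The eligibility criteria require at least 8 couples per cluster and at least two OTs per cluster: 8 / 2 = 4. The sample size section expects on average at least 10 eligible clients for two OTs per institute: 10 / 2 = 5.

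**5. Unlisted OT time.** Assumed: newsletters and website 2 h, forum 1 to 2 h, web reporting 0.5 to 1 h per couple.

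- 4 couples: 2 + 1 + 4 × 0.5 = 5 h, to 2 + 2 + 4 × 1 = 8 h.
- 5 couples: 2 + 1 + 5 × 0.5 = 5.5 h, to 2 + 2 + 5 × 1 = 9 h.
- Range: 5 to 9 h; 5/32 = 16%, 9/32 = 28%.
- If web reporting only replaces usual records: 2 + 1 = 3 h to 2 + 2 = 4 h; 3/32 = 9%, 4/32 = 13%.

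**6. How far the assumptions drive this.** With wider inputs (reporting 0 to 2 h per couple, newsletters 5 to 20 minutes each, website and forum together 0 to 4 h):

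- Low: 4 × 0 + 4 × 5/60 + 0 = 0.3 h per OT.
- High: 5 × 2 + 4 × 20/60 + 4 = 15.3 h per OT.
- Over 15 CI clusters × 2 OTs = 30 OTs: 10 to 460 h.
- At the hypothesised adherence gain of 50 − 20 = 30 percentage points: 0.33/30 = 0.01 to 15.33/30 = 0.51 OT-hours per OT per extra percentage point.

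No corrected ratio can be computed, since the document gives no durations, unit prices or running costs.

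**The case against.** Four objections carry weight.

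- **Running costs.** From the development-only and preparation-only labels a reader might infer that hosting, maintenance and dispatch go uncounted. The document does not support that. The Costs text and the Table 3 footnote both say execution costs are all registered. Short labels against two explicit statements are a conflict to reconcile, not a proven omission.
- **Net time.** A reader might also conclude that the CI arm is certainly under-costed. Electronic treatment reports may replace records that OTs would keep anyway, so the net time on that item could be near zero. Time on newsletters, website and forum is more clearly additional, but could be small.
- **Denominator.** The percentages are shares of assumed OT attendance time. The ratio uses total incremental strategy cost, which also includes the strategy providers, annuitised development, and physician and manager time. The proportional effect on the ratio is unknown.
- **Partial cover.** Table 1 already lists a cost survey for OTs, and this is an article whose survey items are not shown. Usage frequencies are collected, and sensitivity analyses on uncertain parameters are planned.

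These limit the size and certainty of the point but do not remove it. Table 3 is presented as the cost data collected and goes down to newsletter reading and phone calls, so neither condensation nor a materiality threshold readily explains recording reading time for two professional groups and not the third. The frequencies could support an imputation, but the article plans none.

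**Conclusion.** The mismatch is established: four CI elements provided to OTs have no OT time row, against the stated scope and the societal viewpoint. The consequence is conditional. If the table is followed as listed, any net extra OT time is lost from the CI arm alone, which would tend to understate incremental cost and flatter the primary cost per extra percentage adherence.

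The size is not determinable from the document and may be small. The range of 5 to 9 h per OT, or 3 to 4 h if reporting is only displaced, rests on assumed durations throughout. The figure of 4 to 5 couples per OT is not an upper bound, because the Trial Design section expects more referrals in the CI arm and both source figures are minima. The point deserves correction because it affects a primary question, can bias in only one direction, and is cheap to repair.

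**What to change.** 1. Add OT rows to Table 3 at 6 and 12 months for newsletters, website, discussion forum and web-based reporting, collected through the existing OT cost survey. For reporting, ask only for time beyond usual record keeping.
2. Where the time can no longer be collected, value the usage frequencies from the process evaluation with a stated unit time, and vary that time in the sensitivity analyses already planned.
3. List operating costs for the web-based system and website, and dispatch costs for the newsletters, so that these row labels agree with the statement that all execution costs are registered.
4. If any of these items is captured elsewhere or judged negligible, say so explicitly.

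The cost is a few more survey questions, and a ratio that may turn out slightly less favourable to the CI strategy.
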